## Abstract

**Introduction:** Population aging is a global phenomenon that has grown rapidly and progressively all over the world. Interventions that promote health must be studied and implemented to make the aging process be with quality of life. Depression and anxiety are the most common mental health conditions that compromise the quality of life on the elderly and it can cause damage to the autonomy and activities of daily life. Mindfulness training has been shown to improve psychological health and quality of life on adults. Studies involving Mindfulness-Based Interventions (MBIs) with older people are scarce in the literature, but they have been increasing in recent years showing promising results for healthy aging. This trial will investigate the feasibility and preliminary efficacy of an MBI on the quality of life of elderly assisted in the Primary Care.

**Materials and Methods:** A cohort-nested randomized controlled trial with 3 assessment points (baseline, post-intervention and 1-year follow up) will be conducted to compare a MBI program (Mindfulness-Based Health Promotion) to a cognitive stimulation control-group in a Primary Care facility. One-hundred and two older adults will be recruited from a cohort of this facility and they will be randomized and allocated into an intervention group (*N* = 76) and the control group (*N* = 76). The primary outcome evaluated will be the improvement of quality of life assessed by the WHOQOL-BREF and WHOQOL-OLD. The secondary outcomes will be cognitive function, psychological health, sleep quality, self-compassion, and religiosity. Qualitative data will be assessed by focus group and the word free evocation technique. The feasibility of the program will also be evaluated by adherence and unwanted effects questionnaires.

**Discussion:** This cohort-nested clinical trial will be the first mixed-methods study with 3 assessment points which will study the feasibility and preliminary efficacy of a mindfulness-based program for older people in Latin America population. If the findings of this study confirm the effectiveness of this program in this population it will be possible to consider it as intervention that might be implemented as public policy addressed to older people in healthcare systems.

**Clinical Trial Registration:**
www.ClinicalTrials.gov, identifier: NCT03048708. Registered retrospectively on October 11th 2018.

## Introduction

Population aging is a global phenomenon that has grown rapidly and progressively all over the world because of factors such as increased life expectancy and declining birth rates. Brazil has followed this trend with a speed slightly higher than the world growth pattern (1), which has called attention both in scientific research and in the perspective of necessary public policies that promote health and quality of life to attend this demand.

The concept of quality of life is complex to be defined, and it can be interpreted in a multidisciplinary way due to the different cultural, ethical, religious, and people values that influence the way it is perceived (2). The definition of quality of life, according to the World Health Organization Quality of Life Group, is related to “individuals' perception of their position in life in the context of the culture and value systems in which they live and in relation to their goals, expectations, standards, and concerns” (3). From this conceptualization, we can understand that the perception of quality of life has its subjective, multidimensional, and contextual character for each individual.

There is no clear consensus regarding the definition of quality of life in the elderly (4). However, García and Navarro say that quality of life for the older people is a multidimensional concept that is related to their life satisfaction, autonomy, and independence in their execution of their activities of daily living (ADLs) (4). In terms of health assessment, tasks that involve their functional capacity, autonomy, and independence are known as ADLs, and it refers to basic activities related to self-care such as feeding, bathing, and dressing, as also instrumental activities lead an independent life within the community like going shopping (5). Studies show that the better the ADLs, the better the quality of life (6–9).

A longitudinal study published (10) demonstrated that older people who meditated more frequently over 59 weeks between the initiation of an 8-week mindfulness-based intervention (MBI) program and the 1-year follow-up had a greater performance in their ADL than the group that meditated less frequently.

The MBIs were originated from the mindfulness-based stress reduction (MBSR) program. The MBSR was built by Jon Kabat-Zinn et al. at the University of Massachusetts Medical Center (11, 12), and it is an intervention whose effects on health promotion and quality of life have produced several studies worldwide (10, 13–21). Recently, its implementation in primary care (PC) (22, 23) and its benefits with the elderly population (10, 24–31) have been studied.

*Mindfulness* can be defined as a state or trait that refers to the ability to be aware of what happens in the present moment intentionally and non-judgmentally, and it involves two fundamental components: self-regulation of attention and open orientation to one's own experience with curiosity, openness, and acceptance. One of the most used ways to get to this state of mindfulness is through the formal practice of mindfulness meditation within MBI programs (11, 32, 33).

A study has demonstrated that an MBI program has reduced the perception of loneliness in the elderly (24). Loneliness is a risk factor associated with decreased cognitive function, depression, and morbid and unhealthy behaviors in the aging population (34, 35). Depressive and anxiety disorders are the mental health conditions that most compromise the quality of life of the elderly (36, 37). According to Krug et al. (38), physical, cognitive, and social activities reduce the consequence of cognitive decline and can be used as preventive measures.

Several protocols have been developed based on the MBSR aimed at specific samples, such as the Mindfulness-Based Health Promotion (MBHP) (39) program developed by the Mente Aberta – Brazilian Center for Mindfulness and Health Promotion. The MBHP program was inspired by the original MBSR model but adapted to the context of PC and health promotion, and it has been applied in Brazil.

Despite the increasing number of researches investigating the effects of MBIs with the elderly (26, 27, 40–42), they are still scarce, and most are non-randomized and inconclusive, with small sample size and with high risk of bias (43). Thus, more controlled, randomized, and mixed-methods studies involving MBIs with the elderly are needed, especially with experiences of its applications in PC, a core component of healthcare systems, both public and private.

Thus, the aim of this study is to evaluate the feasibility and preliminary efficacy of the MBHP program on quality of life (primary outcome) of older adults assisted in PC comparing to a cognitive stimulation active control group. Our main hypothesis is that the MBHP is feasible and efficacious in promoting quality of life in people older than 60 years, and it will improve psychological health, self-compassion level, sleep quality, religiosity, and score at ADLs and prevent or delay cognitive decline in the elderly (secondary outcomes). Also, we hypothesize that the MBHP is superior to a cognitive stimulation group to promote those benefits.

## Materials and Methods

The “MBHP-Elderly Study” is a randomized controlled trial addressing older people with 3 assessment points (baseline, post-intervention, and 1-year follow-up) nested in a cohort study (the EPIDOSO study) of older adults patients assisted in a PC facility of the “Center for Aging Research” [Centro de Estudos do Envelhecimento (CEE)] of the Universidade Federal de São Paulo—UNIFESP.

One hundred fifty-two participants will be recruited from the cohort and then randomized into the following two experimental groups: (I) MBHP intervention group (76 participants) in which the elderly will have a weekly meeting of an hour and 30 min for 8 weeks to perform the MBI (MBHP protocol) accompanied by extra four 1-h meetings through a maintenance group with all participants after the eighth week (each maintenance session took place fortnightly), totaling a 4-month (16-week) intervention; (II) cognitive stimulation control group (76 participants) of elderly who will take computer-based cognitive stimulation classes for 4 months, once-a-week 1.5-h meetings without maintenance phase, totaling 16 weeks. In both groups, the same assessment for data collection will be applied, and they will be applied in the baseline (T0), post-intervention (T1), and 1-year follow-up (T2). Both interventions will last 16 weeks. However, the reason why the MBHP intervention group will take 12 sessions and the cognitive stimulation control group 15 sessions is because one of the aims in the MBHP intervention is to work on the participants' autonomy in their personal mindfulness practice in daily life through home activities exercises, and we wanted to compare its outcomes with the 4-month weekly meetings of control intervention, which require face-to-face sessions. Study design and participant flow through the trial is shown in Figure 1.

**Figure 1 F1:**
[figure not shown]
Diagram of planned study flow of participants and study design.

We have decided to use an active control group only (instead to an additional waiting-list control group) due to ethical reasons and to facilitate the recruitment for the study, based on previous protocols' experience of our research centers.

The steps of the study will be conducted based on Consolidated Standards of Reporting Trials (CONSORT) guidelines to report clinical studies in a clear, transparent, and comprehensive manner (44). The protocol is reported according to the Standard Protocol Items: Recommendations for Intervention Trials (SPIRIT) statement [(45); Figure 2], and it was approved by the center ethical committees. This study was retrospectively registered under ClinicalTrials.gov NCT03706807 on October 11, 2018.

**Figure 2 F2:**
[figure not shown]
Standard Protocol Items: Recommendations for Interventional Trials (SPIRIT) diagram. ADL, Activities of Daily Living Scale; CDR, Clinical Dementia Ratings; DASS-21, Depression Anxiety Stress Asessment-21; DUREL, Duke Religious Index; MAAS, Mindful Attention Awareness Assessment; MBHP, Mindfulness-Based Health Promotion; Active Control Group, Cognitive Stimulation; MoCA, Montreal Cognitive Assessment; PSQI, Pittsburgh Sleep Quality Index; SCS, Self-Compassion Scale; -T1, Screening and Recruitment; T0, Before Intervention; T1, Post-Intervention; T2, 1-year follow up; WGGA, Wide Geriatric and Gerontologic Assessment; WHOQOL-BREF, World Health Organization Quality of Life–BREF; WHOQOL-OLD, World Health Organization Quality of Life–OLD.

### Sample Size and Power Calculations

The minimum sample for each group was identified as 64 participants to detect a power of 0.80 and an α of 0.05. These calculations were performed using the G^*^Power 3.1 software for comparison between two intervention groups with respect to the mean differences of the scores at each time point of assessment relative to baseline. Therefore, 152 individuals should be randomized to receive one of the interventions (76 in the intervention group, 76 in the control group) assuming a maximum loss of 15%.

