### Instructors

Four mindfulness tutors will lead the MBHP groups—on Mondays, Tuesdays, Wednesdays, and Thursdays, respectively. All of them were already certified by the Mente Aberta – Brazilian Center for Mindfulness and Health Promotion and have at least 2 years of experience leading the MBHP protocol at the time of the study. The Mente Aberta certifying professional training follows the British and Brazilian guidelines for good practices of mindfulness (53). The cognitive stimulation control group will be conducted by an experienced gerontologist of the CSR who had a specific training in the protocol (described in detail below).

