### Recruitment, Procedures, and Randomization

Overall, 152 elderly were recruited from the cohort of the CSR of the Universidade Federal de São Paulo from June 2018 to May 2019. Recruitment was conducted by invitation phone calls to the cohort list. Participants who showed interest in the research were scheduled to visit the center so that one of five researcher assistants would apply a comprehensive geriatric and gerontological evaluation named as Wide Geriatric and Gerontologic Assessment (WGGA), which comprise sociodemographic data and other measures' information needed for the recruitment such as GDS-15 (49–51) and baseline data such as quality of life [World Health Organization Quality of Life (WHOQOL) BREF and WHOQOL-OLD] (59–62) and ADLs, and then the MoCA (63, 64) is applied in order to evaluate cognitive function.

After this first step, a trained gerontologist applies the CDR (47, 48, 52) to evaluate if the participant has dementia or any cognitive impairment. The CDR evaluation requires a caregiver or a relative close to the older adult to be interviewed to inform about his cognition and behaviors (48). The participants who score 0 or 0.5 were included in the study.

After the screening and recruitment, the 152 participants approved in the inclusion criteria will be randomized and allocated into the groups. Married participants who meet the inclusion criteria will be allocated to the same groups; it was decided to do that because some couples need the support from one another to go to the center. The MBHP program group will then be randomized again into other four subgroups (19 participants each) because the MBI group is better availed when smaller. All the groups will follow the same assessment of the research, and the MBHP protocol will be led by instructors certified by Mente Aberta the whole time. The control group will also be randomized and allocated into small groups according to the number of computers in the computer lab (19 participants each).

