Randomization will be implemented using the Microsoft Excel. Each participant will be randomized individually for each of the two groups. The couples will be stratified into the same groups as it was also considered that, if they were allocated to be separated, one could teach another what was taught and then contaminate the sample. All randomization procedures will be made by a statistical professional who will only receive the identification number of the participants and will not interact with them at any time before, during, or after the intervention.

After the randomization, the participants will be invited to attend the CSR for a lecture, which we will inform which group they were randomized to and when the intervention will start. At this moment, we will hand the participants the informed consent in written form to be signed by the interested and the measure scales that were not filled during the screening such as Mindful Attention Awareness Scale (MAAS) (65, 66), Self-Compassion Scale (SCS) (67, 68), Depression Anxiety and Stress Scale (DASS-21) (69, 70), Pittsburg Sleep Quality Index (PSQI) (71, 72), and Duke Religious Index (Durel) (73, 74).

Due to the nature of the intervention, this will be a single-blind study, in which the outcomes assessment and analyses will be blind, but the participants will be aware of their group assignment.

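### The sample size and the named tests treat participants as independent although both arms are taught in classes of 19; for any positive within-class correlation, power at 64 completers per arm is below 80% and the tests reject too often

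*Protocol article*

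**What the plan says.** **Sample size.** Sample Size and Power Calculations states: "The minimum sample for each group was identified as 64 participants to detect a power of 0.80", at an alpha of 0.05. The calculation was done in G*Power, "software for comparison between two intervention groups with respect to the mean differences of the scores at each time point of assessment relative to baseline". The number randomised is 76 per arm, 152 in all, to allow for up to 15% loss. No effect size, sidedness, ICC or design effect is given.

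**Delivery.** Recruitment, Procedures, and Randomization says of the intervention arm: "The MBHP program group will then be randomized again into other four subgroups (19 participants each", and of the control arm: "The control group will also be randomized and allocated into small groups according to the number of computers", again with 19 in each. Four control classes follow from 76/19 = 4; the article does not state that number. Under Instructors, "Four mindfulness tutors will lead the MBHP groups", one weekday each, while one gerontologist runs the control arm. The Cognitive Stimulation Protocol section says that activities are adapted to how each class progresses. The opening of Materials and Methods describes the four MBHP sessions after week 8 as a maintenance group for all participants.

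**Analysis.** Statistical Analysis lists sex, age, schooling, treatment group and time as independent variables. It names repeated-measures MANOVA, paired t or Wilcoxon tests, and Mann-Whitney tests between arms. The only further adjustment offered is for possible moderating variables.

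**The concern.** People taught together share a tutor, a group climate and a pace, so their changes from baseline may be correlated. Classes are formed by randomisation, so this correlation does not come from selection. It arises during delivery, and it still adds to the variance of the difference between arms. A calculation that leaves it out overstates power, and a participant-level test that leaves it out uses too small a standard error and rejects a true null hypothesis more often than 5%.

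The second effect matters more here. The article says that a favourable result could support using the programme as public policy, so the false-positive rate on the primary outcome bears on how the result will be read.

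**Working it through.** **Inputs from the article:** 64 completers per arm, power 0.80, alpha 0.05, 15% loss, 76 randomised per arm, classes of 19.

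**Assumptions, not in the article:** standardised difference d = 0.5, two-sided; class ICC of the change score 0.01, 0.02 or 0.05; 64/4 = 16 completers per class.

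**1. The plan's own figure.** An independent two-sample t-test with d = 0.5, two-sided alpha 0.05 and power 0.80 gives n = 63.8, so 64 per arm; power at 64 is 0.801. A one-sided test at d = 0.5 would need 51, which does not match. Then 64/0.85 = 75.3, so 76. Both stated numbers reproduce, and if d = 0.5 they contain no allowance for clustering (design effect 1).

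**2. Design effect.** DE = 1 + (m − 1) × ICC. With m = 16:
- ICC 0.01: 1 + 15 × 0.01 = 1.15
- ICC 0.02: 1 + 15 × 0.02 = 1.30
- ICC 0.05: 1 + 15 × 0.05 = 1.75

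**3. Variance of the arm difference.** It grows by a factor V. If both arms are clustered equally, V = DE. If only MBHP is clustered, V = (DE + 1)/2, which is 1.075, 1.15 and 1.375.

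**4. Power of a test with the correct variance (normal approximation).** Power = Φ(0.5 × √(64/(2V)) − 1.96). Example, ICC 0.05 in both arms: 0.5 × √(64/3.5) = 2.138, and Φ(0.178) = 0.57. With V = 1 the formula gives 0.807.

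**5. Type I error of the unadjusted test.** 2 × (1 − Φ(1.96/√V)). Example, ICC 0.05 in both arms: 1.96/1.323 = 1.48, giving 13.8%.

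| Assumed ICC | Power, both arms | Power, MBHP only | Type I error, both arms | Type I error, MBHP only |
|---|---|---|---|---|
| 0.01 | 75% | 78% | 6.8% | 5.9% |
| 0.02 | 70% | 75% | 8.6% | 6.8% |
| 0.05 | 57% | 67% | 13.8% | 9.5% |

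**6. No loss.** With 76 per arm and m = 19, ICC 0.01 in both arms gives DE = 1.18 and power Φ(0.5 × √(76/2.36) − 1.96) = 0.81. The loss allowance then absorbs the clustering. At ICC 0.02 and 0.05 the power is 75% and 61%.

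**7. Few classes.** A test on 8 − 2 = 6 degrees of freedom, with 64 per arm and both arms clustered, has power of about 60%, 55% and 44% for the three ICCs. At ICC 0 it already has only 66%, so much of that loss is the price of few degrees of freedom and not of correlation.

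**8. Couples.** If 10% to 20% of participants are in couples with a within-couple correlation of 0.2 to 0.5 (assumed), DE = 1 + share × correlation = 1.02 to 1.10, and power is 79% to 76%.

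**The case against.** **The size is assumed.** Neither d nor the ICC is in the article, and the classes are randomised from one cohort. This stands: the figures are conditional. The direction needs only an ICC above zero, and the article neither states nor defends a value of zero.

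**MBHP classes may not stay fixed.** The maintenance sessions are described as for all participants, and the post-intervention assessment is at the last of them. If the classes are pooled after week 8, the correlation at assessment could be weaker. This stands as a reason why the true figure may lie at the low end.

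**The control arm has one instructor.** Tutor differences therefore cannot separate control classes. This stands, and is why the MBHP-only columns are shown. Adapting activities to each class could still create some correlation, so the two structures bracket the answer.

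**An SAP may add a class term.** It may, since the article condenses a fuller plan and its analysis wording is permissive. An SAP cannot, however, make the published calculation allow for clustering, and the variables and tests already named leave class out.

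**Stronger readings that the article does not support.**
- A reader might infer that 80% power is claimed for 152 people. It is claimed for 64 per arm, 128 in all; 152 includes the loss allowance.
- A reader might take the 6-degrees-of-freedom power as the effect of clustering. It includes a penalty that is present at ICC 0.
- A reader might treat couples as a main driver, or as contradicting individual randomisation. The article states the exception ("The couples will be stratified into the same groups") with its reasons, and the effect on power is small.

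**Conclusion.** The point holds for class clustering. The stated 80% at 64 completers per arm assumes independent participants, while the design puts them in classes of 19 and the named tests have no class term. Under ICCs of 0.01 to 0.05, power is about 75% to 57% with both arms clustered, or 78% to 67% with MBHP alone clustered. Unadjusted type I error is 6.8% to 13.8%, or 5.9% to 9.5%.

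Confidence is high in the direction and limited in the size. The size rests on an inferred d of 0.5, an assumed ICC and 16 completers per class. It is not correct to say that power is below 80% in every case: with full retention and ICC 0.01 in both arms, it stays near 80%.

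**What to change.** 1. **Sample Size and Power Calculations:** state the assumed effect size and sidedness, and replace the single power value with a range over plausible class ICCs, showing both the both-arms and the MBHP-only case.
2. **Statistical Analysis:** make the main between-arm comparison a mixed model with a random class effect, with its variance allowed to differ by arm, and a small-sample degrees-of-freedom correction (Satterthwaite or Kenward-Roger). Because each MBHP class appears to have its own tutor, the term covers class and tutor together.
3. **Data:** record class for every participant, and say whether MBHP classes stayed separate in the maintenance sessions.
4. **Couples:** handle them in a sensitivity analysis, since a couple effect may be barely estimable.

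The cost is a less favourable stated power and wider intervals, partly because eight classes leave few degrees of freedom. No extra participants and no change to delivery are needed.
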